## Abstract

**Background:**

The Onset PrevenTIon of urinary retention in Orthopaedic Nursing and rehabilitation, OPTION, project aims to progress knowledge translation vis-à-vis evidence-based bladder monitoring in orthopaedic care, to decrease the risk of urinary retention, and voiding complications.

Urinary retention is common whilst in hospital for hip surgery. If not properly identified and managed, there is a high risk of complications, some lifelong and life threatening. Although evidence-based guidelines are available, the implementation is lagging.

**Methods:**

Twenty orthopaedic sites are cluster randomised into intervention and control sites, respectively. The intervention sites assemble local facilitator teams among nursing and rehabilitation staff, including first-line managers. The teams receive a 12-month support programme, including face-to-face events and on-demand components to map and bridge barriers to guideline implementation, addressing leadership behaviours and de-implementation of unproductive routines. All sites have access to the guidelines via a public healthcare resource, but the control sites have no implementation support.

Baseline data collection includes structured assessments of urinary retention procedures via patient records, comprising incidence and severity of voiding issues and complications, plus interviews with managers and staff, and surveys to all hip surgery patients with interviews across all sites. Further assessments of context include the Alberta Context Tool used with staff, the 4Ps tool for preference-based patient participation used with patients, and data on economic aspects of urinary bladder care.

During the implementation intervention, all events are recorded, and the facilitators keep diaries.

Post intervention, the equivalent data collections will be repeated twice, and further data will include experiences of the intervention and guideline implementation.

Data will be analysed with statistical analyses, including comparisons before and after, and between intervention and control sites. The qualitative data are subjected to content analysis, and mixed methods are applied to inform both clinical outcomes and the process evaluation, corresponding to a hybrid design addressing effectiveness, experiences, and outcomes.

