### Setting and inclusion criteria

The research team called upon orthopaedic units in university, regional, and local hospitals across Sweden. To avoid excess travel during data collections and enable participation in the intervention, the hospitals furthest north and south were contacted last. All 55 potential sites are equivalent in funding, either run by the public sector or company-driven hospitals with regional procurements. Further, they were considered equal, regardless of providing hip fracture surgery and elective hip replacements or elective hip replacement surgery only. A sample of 20 orthopaedic units was deemed necessary to provide sufficient statistical strength to detect an impending increase in adherence to the guidelines in the intervention group.

The sites were contacted by the research team with information and were engaged as a result of each head of department consenting to the OPTION study. Reasons for declining to participate concerned primarily staffing issues or heavy workload due to the pandemic (in some cases requiring orthopaedic units to transform into COVID-19 units).

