### Power and sample

The study power calculation is based on opportunities to detect an impending increase in adherence to national bladder monitoring guidelines: assuming an absolute increased adherence to the guidelines of 15% (50% in the control group and 65% in the intervention), the required sample size is 227 patients in each arm, with 90% power and two-sided significance level of 0.05 (based on an intracluster correlation coefficient of 0.03). With 10 clusters in each arm and an average cluster size of 70 patients, a total of 1380 patients are needed. Considering a dropout rate of 10%, a total sample size of 1500 is required, providing an average cluster size of 75 patients. With a variance between around 5% and 80% incidence of urinary retention among hip surgery patients, it is difficult to calculate power based on this factor. Yet, considering that it may be 35–40%, the cluster size suggested above will also allow detecting a 15% absolute difference in incidence of urinary retention between the intervention group and the control group post intervention.

Once the units had agreed and the ethics board had approved the trial, the randomisation was performed. To prevent bias in terms of complexity of the patients’ medical status, and influence of clinical training programmes for students in nursing science and physio- and occupational therapy, university hospitals were equally distributed as intervention and control units. Further, two units located in Stockholm, the capital of Sweden, were randomised to either intervention or control. Thus, the randomisation was completed in four steps: university units, units in the Stockholm catchment area, and regional orthopaedic and local orthopaedic units, respectively, drawn from sealed envelopes by an impartial researcher engaged for this procedure whilst monitored over video link by the research team.

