A.Quantitative data regarding urinary retention will be collected from patient records, including bladder monitoring, voiding and healthcare interventions, by means of a structured template [12, 22] at baseline, post completion of the study intervention, and an additional, 1-year follow-up.B.Structured patient record assessment in triangulation with qualitative interviews with a random sample of nursing and rehabilitation staff and managers across all sites [13, 23, 25, 38]. In addition, baseline data collection includes mapping the context, with the Alberta Context Tool (ACT) [39, 40] distributed among all nursing and rehabilitation staff.C.Qualitative interviews post intervention (follow-ups I and II), in addition to voice recordings of all events during the intervention (support programme) [13, 23, 41]. Further, IF teams and managers will be asked to keep notes, by means of an individual, semi-structured reflective diary [42].D.Structured patient record assessment in triangulation with a post-discharge structured survey to all hip surgery patients for voiding difficulties after the hospital episode, self-care management and conditions for participating in accordance with one’s preferences—the latter using the 4Ps tool (Patient Preferences for Patient Participation) [43–45]. Further, data will originate from qualitative interviews with a sample of two patients per data collection point and site, representing the age range and gender distribution among those having had hip surgery.E.The structured patient record assessments at baseline, follow-up I and follow-up II will inform the health economics evaluation.

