### Data analysis

Data from patients’ records, the Alberta Context Tool questionnaire, the patient survey on voiding difficulties, and patient participation will be analysed with statistical analyses [46]. Between-group differences will be analysed using Student’s independent-sample t test for continuous variables, the Mann–Whitney U test for non-normally distributed continuous variables, and a χ2 test for nominal variables.

Qualitative content analysis will be applied for all interviews [47, 48], subsequently transcribed verbatim to text files by a professional service.

All data will be considered in the final mixed methods [49], embedding the process evaluation [50].

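### The named between-arm tests take no covariate, so baseline adherence recorded at all 20 sites is left out of the effect estimate, at a cost in precision and in protection against chance imbalance

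*Protocol article*

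**What the plan says.** The abstract (Methods) announces the quantitative analysis in one sentence: "Data will be analysed with statistical analyses, including comparisons before and after, and between intervention and control sites".

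The Data analysis section is more specific. It opens with "Between-group differences will be analysed using" and lists the independent-sample t test, the Mann–Whitney U test and the χ² test according to the type of variable. It describes no adjusted model, arm-by-time term or use of baseline, and it names no test for the before/after comparison.

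The Data collection section (item A) has record data gathered with a structured template "at baseline, post completion of the study intervention, and an additional, 1-year follow-up". The abstract places the baseline assessment of urinary retention procedures across all sites. The Participants section recruits hip surgery patients at each of the three time points in control and intervention units alike, so the waves are repeated cross-sections of patients within the same sites.

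The Power and sample section sizes the trial on "50% in the control group and 65% in the intervention", "with 90% power and two-sided significance level of 0.05", an ICC of 0.03 and 10 clusters per arm. No baseline correlation enters.

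**The concern.** With only 10 sites per arm, much of the uncertainty in the arm difference comes from which sites happened to fall in which arm. A site's own baseline adherence is the measured variable aimed most directly at that source of noise, and the trial already pays to collect it. Two-sample tests on follow-up data cannot use it.

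Two things are at stake. The first is precision: a wider confidence interval than the data allow. The second is interpretation: if the arms start several points apart by chance, the named analysis carries that gap into the estimate, and readers who see a baseline table will ask how much of the result it explains. Without one primary estimate that uses baseline, that question is left to informal comparison of the before/after results with the between-arm results.

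**Working it through.** **Inputs from the article (Power and sample):** adherence 50% and 65%, two-sided α 0.05, 90% power, ICC ρ = 0.03, 10 sites per arm, mean 75 patients per site before 10% dropout.

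**Assumptions:** m = 75 × 0.9 = 67.5 analysable patients per site in each wave; c, the correlation of site effects between baseline and follow-up, from 0 to 0.9. The article gives neither.

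**1. The plan's own figure.** For two proportions with pooled variance under the null:

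n = [1.96·√(2 × 0.575 × 0.425) + 1.2816·√(0.25 + 0.2275)]² / 0.15² = 226.2, rounded up to 227.

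This matches "the required sample size is 227 patients in each arm". The design effect 1 + (m − 1)ρ is 3.04 at m = 69, giving 2 × 227 × 3.04 = 1380. At m = 70 it is 3.07, giving 1394. The stated 1380 is therefore reproduced to rounding as a follow-up-only, unadjusted comparison.

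**2. Share of noise that lies between sites.** At m = 67.5 the design effect is 1 + 66.5 × 0.03 = 2.995. The between-site share of the variance of a site mean is 67.5 × 0.03 / 2.995 = 0.68.

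**3. Unadjusted, with clustering allowed for.** SE = √[0.4775 × 2.995 / (10 × 67.5)] = 0.0460. A site-level t test with 18 df has power 86.9%.

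**4. Adjusted for site baseline adherence (site-level ANCOVA).** The correlation between a site's baseline and follow-up means is r = mρc / [1 + (m − 1)ρ] = 0.676c. The variance is multiplied by 1 − r². Power uses noncentral t with 17 df.

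| c | r | variance factor | SE | power |
|---|---|---|---|---|
| 0 | 0 | 1.00 | 0.0460 | 86.7% |
| 0.3 | 0.203 | 0.96 | 0.0451 | 88.0% |
| 0.5 | 0.338 | 0.89 | 0.0433 | 90.3% |
| 0.7 | 0.473 | 0.78 | 0.0405 | 93.6% |
| 0.8 | 0.541 | 0.71 | 0.0387 | 95.4% |
| 0.9 | 0.609 | 0.63 | 0.0365 | 97.2% |

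At c = 0 the cost is the single degree of freedom: 86.7% against 86.9%.

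**5. Why the form of adjustment matters.** A raw change score multiplies the variance by 2(1 − r). At c = 0.5 this is 1.32, and power falls to about 76%. At c = 0.7 it is 1.05, with power about 85%. Both are below the unadjusted 87%. With balanced waves, an unconstrained arm-by-wave contrast in a mixed model is this same change-score estimate.

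**6. Size of chance imbalance.** Taking adherence near 50%, the true arm difference at baseline has SD √(2 × 0.25 × 0.03 / 10) = 0.039, or 3.9 points. The probability that it exceeds 5 points in either direction, one third of the 15-point target, is about 20%. This ignores the stratified allocation, which would lower it to the extent that the strata predict adherence.

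**7. If 75 per site is spread over the three waves** (25 per wave, no dropout), power is 69.7% unadjusted, and 71.5% to 76.5% adjusted for c from 0.5 to 0.9.

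**The case against.** The strongest reply is that nothing stated here is invalid. Sites are randomised, so a follow-up-only comparison is unbiased on average and matches the way the trial was sized. The article condenses a fuller plan, and covariate adjustment is often left to the SAP. Randomisation in four steps by hospital type and location already gives some protection against imbalance. The gain depends on a between-wave correlation that the article does not report, and at zero there is none.

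Most of this stands, and it sets the size of the point: lost efficiency and uncorrected chance imbalance, not a biased or wrong comparison. It does not remove the point. The article does not stay silent on method; it names tests, and the tests named cannot use baseline.

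Three stronger readings are tempting, and the article does not support them.

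- *Omitting baseline biases the effect estimate.* Under randomisation it does not.
- *Within-arm change is confounded with pandemic recovery.* The phrase "in some cases requiring orthopaedic units to transform into COVID-19 units" gives a reason why some units declined to take part. It says nothing about the 20 enrolled sites.
- *The trial will judge success by improvement in one arm and not in the other.* The aims frame adoption as a comparison with control sites, the power section sizes a between-arm difference, and the abstract lists the two kinds of comparison without calling them separate or unadjusted. That the arm comparison is unadjusted follows from the Data analysis section; for before/after no method is stated.

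The 87% starting point also presumes an analysis that allows for clustering. The tests as literally named make no such allowance. That is a different matter, and this point would remain after it was settled.

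**Conclusion.** The point holds in a limited form. The between-arm comparison is fixed as unadjusted two-sample tests although the same record data are collected at baseline in every site. The contrast stays valid on average, but it is less precise than the data permit and leaves chance imbalance between 10 and 10 sites uncorrected.

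The potential reduction in variance runs from nothing at zero between-wave correlation to 37% at 0.9. This rests on an ICC of 0.03 and 67.5 analysable patients per site per wave. The article does not say whether 75 per site is per wave; if it is not, power starts lower and the absolute gain is up to about 7 percentage points. The downside is negligible even if baseline proves uninformative, so the change is worth making before the follow-up data are analysed.

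**What to change.** Amend the Data analysis section to name one primary estimate: the difference between arms in guideline adherence at a stated follow-up, adjusted for each site's baseline adherence and respecting the clustering of patients in sites. Either of these forms will do:

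- a site-level ANCOVA of follow-up adherence on arm and baseline adherence; or
- a mixed model on all waves with site as a random effect, site effects allowed to correlate imperfectly between waves, and the baseline mean constrained to be equal across arms.

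Rule out two forms explicitly. An unconstrained arm-by-wave contrast is a change score and can lose power. Fixed site effects in a follow-up model are collinear with arm.

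Apply the same approach to the other record and survey outcomes that are measured at baseline. Report within-arm before/after changes as description, without p-values offered as evidence that the strategy works. State whether 75 per site refers to each wave.

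The cost is a change of wording and one degree of freedom. No new data are needed.

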**Discussion:**

The OPTION trial has a potential to account for barriers and enablers for guideline implementation in the orthopaedic context in general and hip surgery care in particular. Further, it may progress the understanding of implementation leadership by dyads of facilitators and first-line managers.

**Trial registration:**

The study was registered as NCT04700969 with the U.S. National Institutes of Health Clinical Trials Registry on 8 January 2021, that is, prior to the baseline data collection.

Contributions to the literature
Despite guidelines for preventing and managing risks for urine voiding issues associated with hip surgery, the adoption into practice is lagging.This protocol delineates a trial with local facilitator teams across 10 orthopaedic sites supported to facilitate implementation of urinary retention guidelines during a year, whilst 10 control sites have regular access to the guidelines only.The study will investigate the effects of tailored implementation strategies on staff guideline adherence, the incidence of voiding complications before and after the intervention and between intervention and control sites, and orthopaedic patients, staff, and managers’ experiences of evidence-based voiding practice and guideline implementation.

## Background

Hip surgery is a common procedure in healthcare, performed for individuals with a hip fracture or as elective hip arthroplasty. In Sweden, with a population of just over 10 million people, about 18,000 individuals undergo hip fracture surgery each year [1, 2], and another 18,000 people undergo elective hip replacement surgery [3]. Hip surgery exposes the individual to an increased risk for urinary retention from bed rest, lack of privacy when toileting, pain, medication by means of opioids, anaesthesia and intravenous treatment with fluids—that is, factors associated with being an orthopaedic patient as well as known to cause urinary retention [4, 5]. In fact, the incidence of urinary retention in orthopaedic patients is notable: 7–44% of this group of patients are estimated to develop urinary retention prior to, during or post hip surgery [6–10], with studies reporting up to 84% of hip replacement patients having urinary retention [9, 11]. Although adherence to evidence-based practice guidelines would likely facilitate a decrease in urinary retention risks, there are indications that nursing and rehabilitation staff have inadequate knowledge and lack awareness of risks associated with urinary retention and the need for safer voiding care [12, 13].

Two decades ago, many healthcare professionals and decision-makers were roused by reports on the lack of evidence-based practice in healthcare [14, 15]. Despite progress, there are still gaps between what is known as best care and the healthcare provided for patients in certain areas [16]: in cases when urinary retention is not assessed and managed properly, the patient is exposed to a urinary incontinence, a permanent need for indwelling urinary catheterisation, and/or urinary tract infections or sepsis [17]. Though cost-effective and simple measures are available [18, 19], a general recognition of and adherence to these guidelines is lacking [20]. So far, there have been limited activities to address the implementation of these guidelines; such ventures imply local facilitator team and leadership engagement [21].

### Previous studies

The OPTION study originated from a European multi-centre study [13, 22–24] indicating that a earlier hip surgery episode had triggered urinary incontinence among frail older people residing in nursing homes. A subsequent pilot study in two Swedish orthopaedic units indicated that the knowledge and recognition of urinary bladder issues associated with hip surgery had not transferred to the nursing and rehabilitation staff [12]. Whilst a 3-month intervention to facilitate guideline implementation was appreciated and rendered an enhanced awareness of risk factors associated with hip surgery, the reach beyond the local facilitator teams was limited. Rather, the local teams (including a registered nurse, a physiotherapist or an occupational therapist in each site, plus a licensed practical nurse if so desired) engaged in the implementation programme, but for them to facilitate the uptake of evidence on urinary incontinence prevention in their sites, extended support beyond the 3 months with managers’ backing was required [25].

Parallel and later pilot studies in Sweden and Canada also showed that single professional facilitators or teams render some success in guideline implementation, whilst managers enacting as facilitators suffice in other instances—yet neither can singlehandedly address all essential elements [26–28]. Supposedly, a mutual effort is likely needed. Further, these studies emphasise the need to tailor facilitation activities to address the local context, as suggested by concurrent research [29]. Hence, the OPTION project enlists local facilitator teams across the intervention sites, including professionals and first-line managers, to embark on an extended and tailored implementation programme with support of external facilitators on the research team.

## Methods

### Aims

The OPTION trial will evaluate the effects and outcomes of an implementation strategy for evidence-based practice by means of clinical practice guidelines for postoperative bladder distension and urinary retention. OPTION comprises five work packages, as illustrated in Fig. 1. The study hypothesis is that the adoption of guidelines in daily practice and de-implementation of procedures not compatible with evidence-based urinary retention guidelines will increase with local assigned teams including staff and managers guided to facilitate such implementation (compared with control sites receiving no support). Further, the hypothesis includes that the implementation of the national urinary retention guidelines will render increased prevention and detection of urinary retention in patients having hip surgery, leading to a decreased risk for bladder distension and subsequent lower urinary tract symptoms among patients in the study sites randomised to the support programme.

**Fig. 1 Fig1:**
[figure not shown]
The OPTION project work packages: overall focus, and timeline (WP, work package)

The specific aims of each work package of the project are as follows:
To investigate the incidence of urinary retention, bladder distension and complications among hip surgery patients; the procedures to prevent, detect, and manager urinary retention performed by staff; the hip surgery patients’ experience of voiding issues during the orthopaedic care episode, including the conditions for participation in such issues; staff and managers’ experience of guideline implementation in general and in urinary retention in particular; and staff experience of contextual factors known to influence knowledge implementation (WP1).To provide an implementation support programme for the local facilitator teams, including managers, for 12 months to the sites randomised to the intervention (WP2).To explore the outcomes in terms of attitudes and behaviours in terms of urinary retention and voiding care among staff and managers post intervention, including the procedures to prevent, detect, and manager urinary retention performed by staff, comparing the intervention sites with the control sites (WP3).To explore the outcomes in terms of the incidence of urinary retention, bladder distension and complications among hip surgery patients during and after the hospital care episode, and the hip surgery patients’ experience of voiding issues during and after the orthopaedic care episode, including the conditions for participation in such issues (WP4).To evaluate the activities of the support programme in relation to the contextual factors of the orthopaedic sites, and the activities and actors performed across intervention and control sites, respectively, identifying what influenced the process of facilitation implementation and de-implementation of evidence-based urinary retention care. This includes considering contextual factors, such as barriers and enablers for knowledge translation, and the cost associated with adhering to or diverging from guidelines (WP5).

